## Abstract

**Background:**

HIV testing is an essential gateway to HIV prevention and treatment thus controlling the HIV epidemic. More innovative interventions are needed to increase HIV testing among men who have sex with men (MSM) since their testing rate is still low. We proposed an online HIV test results exchange mechanism whereby the one without a certified online HIV report will be asked to test HIV for exchanging HIV report with others. The exchange mechanism is developed as an extension to the existing online HIV testing service system. Through the extended system, MSM can obtain certified online HIV reports and exchange their reports with friends via WeChat. This study aims to assess effectiveness of the exchange mechanism to increase the HIV testing rate among MSM.

**Methods:**

This study will use a cluster randomized controlled trial (RCT) design. Participants are recruited based on the unit of individual social network, the sender and the receivers of the HIV report. An individual social network is composed of one sender (ego) and one or more receivers (alters). In this study, MSM in an HIV testing clinic are recruited as potential egos and forwarded online reports to their WeChat friends voluntarily. Friends are invited to participate by report links and become alters. Ego and alters serve as a cluster and are randomized to the group using the certified online HIV report with exchange mechanism (intervention group) or without exchange mechanism (control group). Alters are the intervention targeting participants. The primary outcome is HIV testing rate. Other outcomes are sexual transmitted infections, sexual behaviors, HIV testing norms, stigma, risk perception and HIV report delivery. The outcomes will be assessed at baseline and follow-up questionnaires. Analysis will be according to intention to treat approach and using mixed-effect models with networks and individuals as random effects.

**Discussion:**

This is the first study to evaluate the effectiveness of an HIV test result exchange mechanism to increase the HIV testing among MSM. This assessment of the intervention will also provide scientific evidence on other potential effects. Findings from this study will yield insights for sustainability driven by communities' intrinsic motivation.

*Trail registration:* ClinicalTrials.gov NCT03984136. Registered 12 June 2019.

**Supplementary Information:**

The online version contains supplementary material available at 10.1186/s12879-021-06484-y.

## Background

Men who have sex with men (MSM) are bearing a disproportionate burden of the global HIV epidemic, with 23% of new HIV infection cases transmitted by gay men and other MSM globally [1]. The situation is similar in China, MSM accounted for 25.5% of new HIV infections [2], and MSM infection rates in China have risen from 0.9% in 2003 to 6.9% in 2019 [3]. HIV testing is one effective way to control HIV infection, which could detect people living with HIV/AIDS and link them to antiretroviral therapy and therefore reduce HIV transmission [4]. In 2014, the Joint United Nations Programme on HIV/AIDS (UNAIDS) promoted the 90-90-90 targets to control the global HIV epidemic. Raising HIV testing uptake and frequency among concentrated populations such as MSM is critical to achieving the first 90-90-90 targets of 90% of all people living with HIV knowing their HIV status [5]. There is evidence that HIV testing in a higher frequency has been associated with lower HIV risk, and is an effective scheme to reduce the HIV infection rate among MSM [6, 7].

However, it is estimated that nearly 25% of MSM living with HIV in the United States were unaware of their infection and 33% in Europe [8, 9]. The testing rates in the above areas are close to the 90% goal but gaps persist, while it is worse in low-and-middle-income countries (LMIC), including China. In China the rate remains low despite a national HIV prevention plan targeting HIV testing for MSM has implemented [10]. Only 38% of Chinese MSM had been tested in the past year and about half of MSM had not been tested for HIV were never tested in their lifetime [11]. More efforts to promote HIV testing are needed to address the poor testing rate among MSM.

To date, there are many interventions that expand the coverage of HIV testing in MSM populations, such as Internet-based interventions that deliver health information through website or mobile applications [12–18], peer-led interventions that recruit MSM peer to transfer intervention information [19–23], community-based interventions that promote large-scale health education in community level [24–26], self-testing [27–32], etc. However, most strategies are targeting health education, mainly to raise the awareness for early HIV testing. Health education, especially the top-down perspective, has been criticized for its preaching style and lack of target population insight [33, 34]. Other strategies like HIV self-testing decrease the barriers to HIV testing uptake but are not able to motivate those who think it is unnecessary to have HIV testing. More importantly, the transmission of existing interventions mainly relies on external incentives, not the internal demand-driven. This means that these interventions may gain satisfactory outcomes during the research period, but become unsustainable after manpower input is terminated. MSM community demand-driven intervention to promote uptake of HIV testing is very few globally.

Disclosure of HIV status before sex is the MSM community spontaneous HIV risk reduction effort [35, 36]. Previous studies reported that MSM tend to selectively engage in anal intercourse with those of the same HIV status [37, 38]. However, the oral notification of one’s HIV status in daily life is not always reliable unless MSM have more convincing ways to inform their sex partners about HIV testing results. Moreover, disclosure of HIV status is not bilateral sometimes if one of them has not gotten HIV tested before. From the perspective of the social exchange theory, an individual's profitable resources are under the control of some other actors, and the pursuit of interests leads the individual to exchange resources with other actors [39]. For the MSM population, knowing sex partners’ HIV status is profitable in reducing the risk of HIV infection. In order to achieve safe sex, MSM disclose and exchange HIV test results with sex partners. When one MSM is unknown about his HIV status, the demand of exchanging the HIV test result with sex partners would drive him to HIV testing.

Based on these considerations, we proposed an online HIV test results exchange mechanism whereby the one without a certified online HIV report will be asked to take the HIV testing in exchange for the other’s certified online HIV report. Introducing HIV test results exchange mechanism into the intervention design not only meets the safe sex need of MSM, but also allows the intervention voluntarily transmitted among MSM, thus effectively and sustainably expands the coverage of HIV testing in this population. To the best of our knowledge, this is the first intervention using the HIV test results exchange mechanism in the world, which is driven from the community demand to promote HIV testing behaviors. We will evaluate the HIV test results exchange mechanism in a two-arm cluster randomized controlled trial (RCT). The primary aim of this study is to test the effectiveness of the intervention to promote HIV testing among MSM. A cluster RCT is used because the HIV test result exchange process occurs in an individual and his friends and the observations can be correlated in these MSM.

## Methods

### Study design

A two-arm, cluster randomized controlled trial is used to evaluate the effectiveness of the HIV test results exchange mechanism on increasing HIV testing behaviors among MSM. The exchange mechanism will be developed in WeChat mini program as an extension to the existing Center for Diseases Control and Prevention (CDC) certified HIV testing service system. HIV testing, other sexual related behaviors and HIV report delivery among MSM who receive certified online HIV results (COHIV) with exchange mechanism (intervention group) and those who receive COHIV (control group) will be compared at baseline, 3, 6 and 9 months (Fig. 1).

**Fig. 1 Fig1:**
[figure not shown]
The schedule of enrolment, interventions, and assessments

### Study setting

#### HIV testing service setting among MSM in Guangzhou

The study will be conducted in Guangzhou, belongs to Guangdong-Hong Kong-Macao Greater Bay Area, which is located in South China. Guangzhou is one of four mega-cities in China, with 15 million population, attracts MSM in China with its tolerant environment towards homosexuality. Because of its forward economic rise, it emerged the earliest internet-based MSM dating in China. The internet-based dating website in Guangdong started from the GZTZ.ORG since 1998, and was run by this MSM community-based organization, Guangzhou Lingnan Community Support Center since 1998 [33–35].

This study will be conducted based on a famous gay-friendly HIV testing service clinic in Guangzhou, which is operated by Guangzhou Lingnan Community Support Center and supported by Centers for Disease Control and Prevention (CDC) in Guangzhou. Almost 60% of HIV testing among local MSM is conducted by this clinic every year (average 10,000 person-times per year).

#### Current WeChat-based HIV testing service system

Besides the above clinic-based testing services, a well-established WeChat mini-program of HIV Testing Service System is developed by this community organization and Guangzhou CDC, serving MSM to make appointments, register and read results report [40, 41].

WeChat was initially invented as an instant messaging app in 2011 and later became a ubiquitous daily use app integration with multi-function for local services [42]. With the growing users of WeChat in China, the number of monthly active users is over 1200 million, the WeChat-based service system was developed in 2013 [43]. Mini-programs are the “sub-applications” within the WeChat ecosystem [44], which has several benefits. Participants will get a native app-like experience without leaving WeChat interface, which enhances user convenience for swift interactions, occupies lower memory space of their smartphones, and enables convenient mini-program sharing through existing WeChat social networks, which provides a foundation for our intervention.

Now the established WeChat-based HIV Testing Service System platform launched at the Guangzhou Lingnan Community Support Center has three modules(Wechat mini-program:查呗). The *Appointment Service* module provides nearby HIV testing service clinics’ information in users’ WeChat interfaces. MSM can choose the gay-friendly clinic and make appointments for the HIV testing service (Fig. 2). MSM arriving at the testing clinic should use WeChat to scan the QR code for registration. Then fill in the basic personal information form in the *Service Registration* module, including nickname, gender, date of birth, occupation, nation, education, phone number, address, and whether to require a certified online HIV report (Fig. 3). Only registered users can proceed to the test service. For the *Smartphone-based HIV Test Results Report Service* module, users will receive their own CDC COHIV in the mini-program after the post-test counseling. The COHIV includes the basic testing information and the test result. The former includes the tester identity (anonymous or upload a photo of the tester taken on-site), test date, test result, test method, testing site, report issuing institution, and the signature of the auditor, explanation about the meaning of the “window period” of HIV testing and the meaning of negative results (Fig. 4).

**Fig. 2 Fig2:**
[figure not shown]
The WeChat-based HIV Testing Service System (Appointment Service module). Images depicted in this figure are screenshots of the appointment service module in the WeChat mini-program

**Fig. 3 Fig3:**
[figure not shown]
The WeChat-based HIV Testing Service System (Service Registration module). Images depicted in this figure are screenshots of the service registration module in the WeChat mini-program

**Fig. 4 Fig4:**
[figure not shown]
The WeChat-based HIV Testing Service System (Smartphone-based HIV Test Results Report module). The image depicted in this figure is the screenshot of the smartphone-based HIV test results report in the WeChat mini-program

### Participants

The potential participants are MSM who received exchangeable or regular online COHIV. The recruitment is based on the unit of an egocentric social network (Fig. 5), which includes one core member (ego) and several network members (alters) who connect to this core member. In this study, the ego is defined as one MSM people who tests HIV at the Lingnan Community Support Centre clinic and shares his COHIV via WeChat mini-program to his WeChat contactors, while alters are those contactors who receive and read the shared report. An ego and his alters are considered as a cluster in this trial. Our intervention is targeting alters, whereas egos are the recruiters of MSM alters.

**Fig. 5 Fig5:**
[figure not shown]
A cluster unit of egocentric social network

#### Inclusion and exclusion criteria

Egos who are (1) aged 18 years old, (2) had anal sex with men, and (3) HIV negative (online COHIV are not available for HIV-positive individuals since there is a special legal protecting their privacy) will be included. Individuals are excluded as egos if they do not use WeChat.

The inclusion criteria of alters include (1) aged 18 years old, (2) had anal sex with men, (3) plan to live in Guangzhou in the next year, and (4) HIV unknown or negative. Individuals are excluded as alters if they cannot complete the questionnaire due to any reasons. During the post intervention stage, if a alter is tested as HIV positive, his follow-up will be terminated.

#### Egos recruitment

Egos will be recruited at the Lingnan Community Support Centre clinic. MSM who come to HIV testing and meet all the inclusion criteria will be invited as the ego during the post-test counseling. The counselor will explain the difference between HIV reports with and without exchange mechanism in detail. The MSM who agree to participate as the recruiters will complete a written consent (Additional file 1). Each ego will be randomly assigned to the intervention or control group by mini-program. The egos in the intervention group will receive the COHIV with exchange mechanism through the WeChat mini-program while the egos in the control group will receive HIV report without exchange mechanism. Egos will be informed by counselors they can share their HIV reports with friends via WeChat mini-program to recruit alters.

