### Randomization, blinding and allocation

Clusters will be blocked by egos and allocated 1:1 to the two groups. The random allocation sequence will be generated by using an electronic random number table and embedded in WeChat mini-program. The sequence will be concealed until the intervention is assigned. Egos will be randomly and automatically assigned to the intervention or control group by the mini-program once the online certified HIV report is sent to their WeChat. As a cluster, the group assignment of an alter is determined by his ego. This will be an open-label study in view of the intervention nature, while the statistician and the clinic staff are blinded. Contamination will be avoided by technical means in which alters in one group cannot open the shared link from egos in the opposite group.

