### Sample size and statistical power

We calculated our sample size using intracluster correlation, number of outcomes, expected effect size, and the power of the study. We assumed that the intracluster correlation coefficient (ρ) was 0.2, that each social network will consist of no less than 2 alters, and that the HIV testing rate among alters in the control group during the three-month follow up will be 20%. Setting the acceptable level of significance at 0.05 and expected effect size as 10%, 176 social networks (176 egos and 352 alters) are needed in each group to identify the effect with 80% power. Assuming 30% loss of follow-up, we plan to recruit 252 egos and 504 alters in each group.

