### Statistical analysis

Intent-to-treat analysis will be used to compare the outcome as well as the baseline characteristics of participants between the two groups. For the analysis of primary and secondary outcomes, mixed effect models with networks and individuals as random effects will be used to account for the clustering effect. In the main analysis, the fixed effects for the intervention group, visit number, the intervention group-by-visit number interaction will be included in the model without covariates adjustment. Appropriate link function and distribution will be used. The consistency of treatment effects on the primary outcome will be explored in predefined subgroups, including age, education, level of HIV stigma, number of COHIV received by alter, whether the alter received COHIV from his sexual partner, whether the alter exchanged COHIV with the ego, whether the alter received COHIV screenshot, whether the alter had casual partners, whether the alter had UAI with casual partners.

In the supplementary analysis, models with adjustment for age, education, UAI in the past three months, and other HIV-related health promotion received in the past three months will be performed. Secondly, models with missing data imputation will be also conducted. Missing data will be imputed using the multiple imputation approach. The above analyses are used to compare with the main analysis result to determine the robustness of the intervention effect. All the tests will be conducted using 2-sided tests at 0.05 level of significance.

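### Under the plan as written, an enrolled alter who tests negative at the recruiting clinic could be randomised again as an ego, so the claim to avoid contamination is not secured

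*Protocol article*

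**What the plan says.** All references are to the protocol article.

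- **Who becomes an ego.** Egos recruitment: "MSM who come to HIV testing and meet all the inclusion criteria will be invited as the ego". Each ego who consents is then randomised by the mini-program.
- **Ego criteria.** Inclusion and exclusion criteria: adult age, anal sex with men and a negative HIV result. The sole exclusion is "Individuals are excluded as egos if they do not use WeChat". Alters share the age and behaviour criteria and must be HIV negative or of unknown status; their only exclusion is inability to complete the questionnaire. Neither list mentions a man's other role in the trial.
- **Safeguard.** Randomization, blinding and allocation: an alter takes his ego's arm, and contamination is to be prevented because "alters in one group cannot open the shared link from egos in the opposite group".
- **Route to the clinic.** The two intervention sections direct alters in both arms to the same appointment module. The study setting section adds: "Almost 60% of HIV testing among local MSM is conducted by this clinic every year".
- **Analysis.** Statistical analysis: intention to treat, with mixed models that have network and individual random effects and terms for group, visit and their interaction.

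**The concern.** The trial sends alters to be tested, and the place where many would test is also the place where egos are recruited and randomised. A control alter could leave the clinic holding an exchangeable report, and an intervention alter a regular one, during his own follow-up. Under Egos recruitment the counsellor also explains both report types when inviting a man, so a control alter could learn of the exchange mechanism even if he declines to be an ego.

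Two things are at stake. The later contrasts (6 and 9 months) could be attenuated, because the second allocation follows a test. And networks that the model treats as separate could be linked through men who are an alter in one and the ego of another.

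**Working it through.** **1. Does the text allow it?** Take an alter who books through the module, attends the recruiting clinic and tests negative.
- He is an adult MSM who met the matching alter criteria, he is HIV negative, and he uses WeChat, since he was reached through it. Every ego criterion is met and the one exclusion does not apply.
- He is therefore to be invited and, if he consents, allocated when his report is issued. No sentence exempts him or says that he keeps his arm.
- The link block governs what an alter can open from other men. It does not govern his own report or the counselling. It is also worded for alters only, so it does not clearly cover an ego who opens another ego's link.

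**2. The plan's own sample size.** Inputs from Sample size and statistical power: 20% v 30%, two-sided 0.05, 80% power, intracluster correlation 0.2, 2 alters per network, 30% loss.
- Two proportions, pooled variance: 293.15 per arm.
- Design effect 1 + (2 − 1) × 0.2 = 1.2; 293.15 × 1.2 = 351.8, so 352 alters in 176 networks.
- 176 / 0.70 = 251.4, so 252 egos and 504 alters per arm.

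The stated figures reproduce. They assume no crossing, and the inflation covers loss to follow-up only.

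**3. Extreme upper bound.** Assume every alter who tests in a three-month window does so at this clinic with probability 0.60, tests negative, is invited and consents, and that half are allocated to the other arm.
- Intervention: 504 × 0.30 × 0.60 = 90.7; half = 45 (9.0%).
- Control: 504 × 0.20 × 0.60 = 60.5; half = 30 (6.0%).

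**4. Scaled to the recruitment target.** The trial needs 2 × 252 = 504 egos. The clinic does about 10,000 person-times a year, or 2,500 a quarter.
- Alters' share of tests: (90.7 + 60.5) / 2,500 = 6.0%.
- Dual-role men among 504 egos drawn in proportion: 504 × 0.0605 = 30.5; half in the other arm = 15.2.
- 15.2 / 1,008 alters = 1.5%.

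This assumes that all alters are enrolled from the start, which overstates it. If only half of randomised egos go on to recruit, so that 1,008 are randomised, the figure doubles to 3.0%.

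**5. What crossing could do to the contrast.** Worst-case assumption: a man who crosses takes on the other arm's testing rate. Difference = 10 points × (1 − q_I − q_C), where q is the share crossing in each arm. Power uses 352 / 1.2 = 293.3 effective alters per arm.

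| Scenario | q_I | q_C | Difference | Power |
|---|---|---|---|---|
| None | 0 | 0 | 10.0 points | 80% |
| 504 egos randomised | 1.8% | 1.2% | 9.7 points | 78% |
| 1,008 egos randomised | 3.6% | 2.4% | 9.4 points | 75% |
| Extreme upper bound | 9.0% | 6.0% | 8.5 points | 66% |

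These are illustrations on stated assumptions, not figures from the documents. They describe a later window of the same size, not the window in which the triggering test took place.

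**The case against.** The strongest reply is that the article is silent on dual-role men and does not prescribe re-randomisation. The mini-program must already know each alter's arm for the link block to work, and it may honour that arm when it allocates. This stands in part: a second allocation is possible, not certain. But the written rule is affirmative (testers who qualify are invited, and every ego is randomised), and the article claims that its safeguard prevents contamination. On the text, it does not close this route.

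Further points stand and limit the claim:

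- **Size.** Six to nine per cent crossing is a tempting reading, but it takes about five times the planned egos (2,500 / 504 = 4.96). It also applies the clinic's share to an outcome that includes self-testing. At full uptake the clinic would fill 504 places in about 18 days (504 / 10,000 × 365), before most alters had tested. No passage says that ego recruitment stays open to nine months.
- **Timing and mechanism.** The three-month contrast used for the sample size is largely untouched, since the triggering test precedes the second allocation. The intervention acts on men who receive a locked report; a man who has just tested already holds his own.
- **Standard errors.** A reader might infer that they are too small. That is not shown: outcomes come from alters, a dual-role man can be counted once in his first network, and same-arm and opposite-arm links can act in different directions.
- **Bias.** Because testing is the trigger, crossing would be unequal between arms if the intervention works. Under intention to treat this points to attenuation rather than a false positive.

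**Conclusion.** The point holds as a gap in the allocation rules. An enrolled alter who tests negative at the recruiting clinic qualifies as an ego and could be randomised to the opposite arm, and an ego could enrol as another ego's alter. The link block does not cover the report a man is issued himself or the counsellor's explanation, so the absence of contamination is asserted but not secured.

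It would go too far to say that alters are randomised again as a matter of course, or that the separation of arms fails. The documents support a possibility. The likely effect is some attenuation at 6 and 9 months and some linkage between clusters that may misstate standard errors.

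The documents do not fix the size. About 1.5% of alters crossing is a reasonable illustration if 504 egos are drawn in proportion from about 2,500 quarterly tests and all alters are enrolled from the start; 45 and 30 men is an extreme upper bound. The change is worth making because it is cheap and protects the later contrasts.

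**What to change.** Have the mini-program check the WeChat account before allocation, and state the rule in the eligibility and randomisation sections:

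- A man already enrolled as an alter is not randomised. He keeps the report type of his original arm and founds no new trial cluster.
- A man enrolled as an ego cannot be enrolled as an alter.
- Each alter is analysed in the first cluster he joined.

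The cost is one rule in the allocation code and one added eligibility line. The link block already requires the system to recognise an alter's arm, so the check should need little new machinery. The downside is slightly fewer eligible egos. The check does not by itself stop a control alter hearing about the exchange mechanism at the clinic; running it before the counsellor's invitation would deal with that too.
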